**Secondary Objectives:**

Secondary Objective 1: To determine whether cathodal right cerebellar tDCS combined with SFA will improve trained naming, discourse, and functional communication skills in participants with chronic aphasia.

**Hypothesis** 1a. 15 sessions of cathodal cerebellar tDCS plus SFA will be associated with greater improvement in naming trained pictures compared to sham plus SFA.

**Hypothesis** 1b. 15 sessions of cathodal cerebellar tDCS plus SFA will result in greater improvement in discourse (as measured by change in total content units (CU) and syllable per CU in picture description) compared to sham plus SFA.

**Hypothesis** 1c. 15 sessions of cathodal cerebellar tDCS plus SFA will result in greater improvement in functional communication skills (as measured by change in Communication Activities of Daily Living–CADL-3, Holland et al., 2018) compared to sham plus SFA.

**Secondary Objective 2**: To determine whether cathodal right cerebellar tDCS combined with SFA will improve 3 outcomes measures from the Research Outcome Measurement in Aphasia-Core Outcome Set (ROMA-COS, Wallace et al., 2018) at baseline, 1-week post treatment, and follow up time points: The Western Aphasia Battery-Revised (Kertesz, 2007) will be administered as a part of the baseline testing. We will also assess changes in emotional well-being (measured by General Health Questionnaire (GHQ, Goldberg & Hillier, 1979) and quality of life (measured by Stroke and Aphasia Quality of Life Scale (SAQOL, Hilari et al., 2003).

**Hypothesis**: 15 sessions of cathodal cerebellar tDCS plus SFA will result in greater improvement on the WAB-R, GHQ, and SAQOL compared to sham plus SFA.

**Secondary Objectives 3:** To identify whether neural (functional and structural) biomarkers and linguistic characteristics can predict response to cerebellar stimulation and SFA treatment.

**Hypothesis**: Baseline resting state functional connectivity, structural connectivity, lesion volume and site, overall aphasia severity, and naming severity will predict response to cerebellar tDCS treatment with SFA or SFA treatment alone. This exploratory aim may identify stroke patients who are mostly likely to benefit from cerebellar tDCS and/or SFA. This result may have significant implications for designing a Phase III randomized controlled trial.

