Hypothesis 1b: For secondary outcomes, we hypothesize that cathodal cerebellar tDCS results in greater improvement in trained picture naming, greater improvement in discourse (as measured by total content units (CU) and syllable per CU in picture description) and greater improvement in functional communication skills (as measured by change in Communication Activities of Daily Living–CADL-3) compared to sham.

Statistical Analysis: We will evaluate the effect of tDCS on naming trained items, discourse and functional communication skills. In addition, we will also evaluate the effect of tDCS on WAB-R Aphasia Quotient, SAQOL, and GHQ.The analyses will follow similar approach to Aim 1a.

Aim 2: To identify whether neural (functional and structural) biomarkers and linguistic characteristics can predict response to cerebellar stimulation and SFA treatment.

Hypothesis2: Baseline resting state functional connectivity, structural connectivity, lesion volume and site, and overall aphasia severity and naming severity will predict response to cerebellar tDCS treatment.

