Statistical analysis for Aim 2**:** This analysis considers moderation of treatment effects by pre-treatment baseline characteristics. The pre-treatment baseline characteristics include the following: Imaging: Structural (lesion volume, site, FA, MD), Functional (Fisher transformed connectivity values (*z* scores); Linguistic: (Aphasia Severity score as assessed by WAB-R, Naming severity score assessed by PNT). As in Hypothesis 1, we will consider both a conservative approach, using standard contrasts and median splits on the moderating variables as well as a mixed model functional approach. That is, we will split moderating measures, such as the rs-fMRI Fisher Z-transformed measures of connectivity at the median values, then will test the hypothesis that the tDCS response difference varies between the below median values and the above. A standard t-test contrast approach will be adjusted for multiplicity using Bonferroni corrections given that we will separately analyze potential treatment moderators. We will focus on most proximal post treatment outcomes as our primary test, as the power for detecting moderation will likely be the greatest where the treatment effect is strongest. Our second approach will use a fully model based approach that will be able to incorporate multiple moderators simultaneously. This will not require dichotomizing the moderating variables and it will model the relationship non-parametrically. We build on the functional mixed model approach outlined before. Consider building on our model as Y_ijk_ = u_ik_ + x_i_ B + f_k_(j, x_i_) + e_ij_ where here x_i_ is a vector of pretreatment characteristics of interest, such as a collection of lesion volumes or inter-regional Fisher Z-transformed connectivity, i is subject, k is treatment status and j is sampling occasion (time), f_k_(j, x_i_) is the non-parametric interaction effect between treatment status and the potential interaction moderating variables. Note that the function f_k_(j, x_i_) is now a function of both time and baseline participant characteristics. Therefore, we will follow our testing strategy as before. However, of interest is whether f_2_ – f_1_ is flat with respect to dependence on xi. Specifically, consider the simpler model where Y_ijk_ = u_ik_ + x_i_ B + q_k_(j) + e_ij_ where note that the treatment effect, represented by q_k_(j) in the simpler model, does not depend on the moderating variables. Testing between the more complex and simpler models is a test of whether the treatment effect is influenced by the moderating variables. Inference will be performed via the bootstrap. Of note, flatness f_2_ – f_1_ with respect to the moderating variables is a strong null. We will also consider a weaker null under linear separability: f_2_(j, x_i_) = g_k_(j) + h_k_(x_i_). Here the non-parametric treatment function allows for a non-linear effect of the potential moderating variables where they do not have any actual interaction with the treatment effect. While this overall approach is complex, it offers a complete picture of treatment response over time and the impact that moderating variables have. In addition, the model allows us to fit much more complex potential relationships between the impact of treatment and the moderating variables and allows us to consider the moderating variables simultaneously. To summarize the approaches, we will proceed in this order

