
1. T-test comparing the treatment effect across median splits of the moderating variables performed separately, one at a time.
2. A non-parametric modeling approach using spline based linear models testing whether the potential moderating variables interact with the treatment effect over time. We will consider two variations of this approach:
   1. One that assumes linearity
   2. One that assumes non-parametric functions

Sample Size Determination

We used the data from the PI’s K99 study (crossover trial) to estimate the variability of untrained naming score. 52 participants (26 per group) will give us 80% statistical power to detect 0.7 SD difference in change in accuracy of naming untrained items at 1-week post treatment between the study arms. This was done using Wald test for group assignment coefficient in linear regression at 0.1 level of statistical significance. The effect size (0.7SD) is a bit conservative compared to the difference observed on group comparison for 21 participants (10 in tDCS and 11 in sham) in the K99 data, when the tDCS was administered in Phase 1. We propose to enroll 60 participants to account for 10% attrition.

Missing Data

*The analyses will follow the Intention-to-treat (iTT) principle where participants are analyzed based on the group to which they are randomized regardless of early termination, missing data or errors in randomization detected post hoc. To minimize possible biases, analyses will be by intention to treat; any missing data will be addressed with the technique of multiple imputation (Ball et al., 2002; Rubin, 2009), generally recognized as best for handling missing data (Little et al., 2012).*

1. *Early stopping rules. N/A*

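### Aim 2 adjusts the separate moderator t-tests by Bonferroni, although Holm's step-down rule gives the same family-wise error control and never rejects less; the gain is modest

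*Protocol*

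**What the plan says.** The statistical analysis for Aim 2 in section 7 of the protocol describes two approaches.

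- **Separate tests.** The first is introduced with "we will consider both a conservative approach, using standard contrasts and median splits on the moderating variables". Each moderator is split at its median, and the treatment difference is compared between the halves, one moderator at a time. The multiplicity rule is explicit: "A standard t-test contrast approach will be adjusted for multiplicity using Bonferroni corrections given that we will separately analyze potential treatment moderators".
- **Joint model.** The second is introduced with "Our second approach will use a fully model based approach that will be able to incorporate multiple moderators simultaneously". It does not dichotomise the moderators. The sentence "Inference will be performed via the bootstrap" follows the comparison of the more complex and the simpler functional model, so it belongs to this approach.

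The candidate moderators are listed as "Imaging: Structural (lesion volume, site, FA, MD), Functional (Fisher transformed connectivity values" plus two linguistic scores, WAB-R severity and PNT naming severity. Hypothesis 2 in section 7 states that "lesion volume and site, and overall aphasia severity and naming severity will predict response to cerebellar tDCS treatment", alongside functional and structural connectivity. Under Secondary Objective 3 in section 2 the aim is described as exploratory: "This exploratory aim may identify stroke patients who are mostly likely to benefit from cerebellar tDCS and/or SFA".

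The protocol gives no number of tests, no significance level and no power for Aim 2. The only level it states is for the primary sample size, "at 0.1 level of statistical significance".

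**The concern.** When several moderators are tested separately, Bonferroni holds every test to the level divided by the number of tests, however many have already been rejected. Holm starts at the same threshold and relaxes it after each rejection. The family-wise guarantee is identical and needs no independence between the tests, so nothing is bought by staying with Bonferroni.

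At stake is the number of true moderators that Aim 2 identifies, which the protocol wants for designing a Phase III trial. Power is already scarce. Enrolment of 60 with 10% attrition leaves 54 participants, each contrast splits them into four cells, and MRI is done only in those who consent and have no contraindication.

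**Working it through.** **Plan's own figure.** The only power statement concerns the primary comparison. With a two-sided level of 0.10, 80% power and 0.7 SD, n per arm = 2 × (1.645 + 0.842)² / 0.7² = 25.2, so 26 per arm. The noncentral t gives 80.1% power with 26. The stated 52 reproduces, but it does not bear on Aim 2.

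**Inputs for Aim 2**

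- Number of tests: 7, if each named measure is one test (lesion volume, site, FA, MD, connectivity, WAB-R, PNT). Assumed; more if several connections or regions are tested.
- Participants: 60 × 0.9 = 54, or 54 / 4 = 13.5 per cell. This follows from the protocol but is an upper limit for the imaging moderators.
- Family-wise level: 0.05 and 0.10, assumed.
- Moderation (difference in treatment effect between the halves): 0.7, 1.0 and 1.4 SD, assumed.
- Correlation between test statistics: 0.35, assumed.

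**Step 1: thresholds.** Bonferroni uses level/7 throughout. Holm orders the p-values and uses level/7, level/6, …, level/1, stopping at the first failure. At 0.10:

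| Step | 1 | 2 | 3 | 4 | 5 | 6 | 7 |
|---|---|---|---|---|---|---|---|
| Bonferroni | 0.0143 | 0.0143 | 0.0143 | 0.0143 | 0.0143 | 0.0143 | 0.0143 |
| Holm | 0.0143 | 0.0167 | 0.020 | 0.025 | 0.033 | 0.05 | 0.10 |

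No Holm threshold is below Bonferroni's, so every Bonferroni rejection is kept. The first step is the same, so the chance of at least one rejection is the same.

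**Step 2: Bonferroni power for one moderator.** The standard error of the contrast is √(4/13.5) = 0.544 SD. The non-centrality is 0.7/0.544 = 1.29, 1.0/0.544 = 1.84 and 1.4/0.544 = 2.57. Against the normal critical value 2.45 (level 0.10/7), power is 12.2%, 27.0% and 54.9%. Against 2.69 (level 0.05/7) it is 8.0%, 19.7% and 45.3%.

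**Step 3: Holm against Bonferroni.** I simulated 200,000 sets of seven equally correlated normal statistics per setting. Average power per true moderator, Bonferroni → Holm:

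| Level | Moderation | 2 real | 4 real | 7 real |
|---|---|---|---|---|
| 0.05 | 0.7 SD | 8.0 → 8.2% | 8.1 → 8.6% | 8.0 → 9.1% |
| 0.05 | 1.0 SD | 19.7 → 20.2% | 19.7 → 21.1% | 19.6 → 23.5% |
| 0.05 | 1.4 SD | 45.4 → 46.4% | 45.4 → 48.7% | 45.2 → 54.9% |
| 0.10 | 0.7 SD | 12.3 → 12.6% | 12.2 → 13.1% | 12.2 → 14.5% |
| 0.10 | 1.0 SD | 27.0 → 27.8% | 27.0 → 29.3% | 27.0 → 33.3% |
| 0.10 | 1.4 SD | 54.6 → 55.9% | 54.7 → 58.9% | 54.8 → 66.9% |

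The smallest gain came out at 0.1 or 0.2 points depending on the run.

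**Step 4: chance of finding at least one true moderator.** At 0.10 and 1.4 SD this is 73.8% against 73.9% (two real), 87.8% against 87.9% (four real) and 94.3% under both rules (seven real). Holm's error among the null moderators stayed within the nominal level, for example 7.7% at 0.10 with two real at 1.4 SD.

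**Step 5: sensitivity of the absolute figures.** With 13 per cell and a t distribution on 48 df, Bonferroni power at 1.4 SD is 39.7% (level 0.05) and 49.8% (level 0.10). The normal figures above are therefore somewhat high. Holm's second-step threshold then gives 41.9% and 52.2% with 7 tests, but adds only 0.2 to 0.6 points with 20 to 50 tests.

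**The case against.** The strongest reply is that nothing here is wrong. Bonferroni is a valid correction, the protocol itself calls this approach conservative, the aim is exploratory, and a joint model without dichotomising runs alongside. All of that stands, and it is why the point is only a refinement. It gives no reason to prefer Bonferroni, because Holm carries the same error guarantee.

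Three stronger readings are tempting, and the documents do not support them.

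- **Aim 2 discards substantial power.** The 12-point gain needs all seven moderators real at 1.4 SD, twice the 0.7 SD main effect the trial is sized for. If the moderation acted in the tDCS arm only, with within-cell SD 1, each split would have squared correlation 0.7²/(1 + 0.7²) = 0.329 with response. If the moderators were correlated 0.35, the seven together would explain 7 × 0.329/(1 + 6 × 0.35) = 0.74 of that arm's variance. Effects shared across both arms would make the case less extreme, but it remains very favourable.
- **The protocol hypothesises that every listed characteristic is a moderator.** Hypothesis 2 in section 7 can be read that way. The hypothesis under Secondary Objective 3 also covers response to SFA alone, which is prognosis and does not imply an interaction with treatment.
- **The planned bootstrap could supply a step-down max-T adjustment.** That bootstrap is for the model comparison, not the t-tests. Max-T would be a new procedure with only approximate error control at this sample size. With 7 tests at level 0.05 its single-step form gains 0 to 2 points for underlying moderator correlations of 0 to 0.5, and it gains materially only when moderators are strongly correlated, which the protocol does not report.

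The median split costs more than the choice of adjustment. At level 0.05 with 7 Bonferroni tests, 13 per cell and 1.4 SD, a normally distributed moderator kept continuous gives about 64% power against 40%. The joint model already avoids that loss.

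**Conclusion.** The point holds as a modest, free improvement. Bonferroni is valid for the separate moderator tests, but Holm dominates it. The benefit is in how many true moderators are identified, not in whether any is. In the most favourable case the expected number rises from 3.8 to 4.7 of seven (7 × 0.548 and 7 × 0.669); with two real moderators the gain per moderator is at most about 1.3 points.

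These sizes rest on the assumed 7 tests, 13.5 per cell, correlation 0.35, levels of 0.05 to 0.10 and moderation of 0.7 to 1.4 SD. Fewer participants will have imaging data, so absolute power for those moderators will be lower. That Holm dominates Bonferroni needs none of these assumptions.

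**What to change.** In section 7, statistical analysis for Aim 2, replace the reference to Bonferroni corrections with *Holm step-down adjustment*, applied at the same family-wise level to the same set of separately tested moderators.

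This costs one phrase in the protocol and a standard software option, with no extra participants or data. The one drawback is that simultaneous confidence intervals matching Holm are less simple than Bonferroni intervals.

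### The second-step model comparison in Aim 2 is not a pure test of moderation: a variable that predicts improvement equally in both arms can make it reject

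*Protocol*

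**What the plan says.** Section 7 of the protocol (Statistical analysis for Aim 2) plans two steps. The first splits each moderator at its median and tests whether the tDCS effect differs between the halves, one moderator at a time, with a Bonferroni correction. The second is model-based and can take several moderators together.

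For the second step the fuller model is "Y_ijk_ = u_ik_ + x_i_ B + f_k_(j, x_i_) + e_ij" and the simpler one is "Y_ijk_ = u_ik_ + x_i_ B + q_k_(j) + e_ij". Here x holds baseline characteristics, k is the arm and j the occasion. The stated aim is correct: "of interest is whether f_2_ – f_1_ is flat with respect to dependence on xi". The text then makes it specific through the two models: "Testing between the more complex and simpler models is a test of whether the treatment effect is influenced by the moderating variables". On method it adds "Inference will be performed via the bootstrap".

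A weaker null follows, in which the function separates into g_k(j) + h_k(x). It is described as allowing non-linear effects of the moderators "where they do not have any actual interaction with the treatment effect".

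Secondary Objective 3 (Section 2) hypothesises that the same baseline variables "will predict response to cerebellar tDCS treatment with SFA or SFA treatment alone".

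**The concern.** A moderation test should ask only whether the difference between arms depends on x. The two printed models differ by more than that. In the simpler model x can do one thing: shift the score linearly, by the same amount at every occasion. Any x-by-time or curved x effect shared by both arms therefore counts against the simpler model and is then read as moderation.

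The protocol itself expects shared effects of this kind. Secondary Objective 3 allows for prediction of response to SFA alone. Section 4 excludes people averaging above 140/175 on the baseline PNT because they have little room to improve. That links baseline naming to improvement regardless of arm, and baseline PNT is one of the listed moderators.

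Aim 2 is meant to inform the selection of patients for a Phase III trial. A rejection in this second step cannot separate a patient who improves more with any therapy from one who benefits more from tDCS.

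**Working it through.** **Inputs from the protocol.** The two models and the separable form (Section 7, Aim 2). Occasions labelled 0, 1, 3, 6 (Section 7, secondary analysis under Aim 1). Assessments at baseline, 1 week and 1, 3 and 6 months (Section 4). 26 per arm, 0.7 SD, 80% power, level 0.1, 60 enrolled for 10% attrition (Sample Size Determination).

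**Assumed.** The strength of x, the variance components, and a nominal 5% level, since none is stated for this test.

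**The plan's own figure.** None is given for Aim 2. The primary sample size reproduces: 2(1.645 + 0.842)² / 0.7² = 12.37 / 0.49 = 25.2, so 26 per arm and 52 in all. 60 × 0.9 = 54. The simulations use 52 or 54.

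**1. Counter-example.** Let f_1 = f_2 = a·x·t(j), with t = 0 at baseline and 1 afterwards. Then f_2 − f_1 = 0 for every x: no moderation. The effect of x is B at baseline and B + a later. The simpler model allows a single B, so it is false whenever a ≠ 0. Likewise f_1 = f_2 = c·x² gives no arm difference, but the simpler model has only a linear term. Bootstrap inference does not change which null is tested.

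**2. Counting terms** (linear x, five visits). Fuller model: 10 arm-by-visit means + 10 arm-by-visit slopes on x = 20. Simpler model: 10 + 1 = 11. Difference: 9 terms, of which 4 are x-by-time common to both arms and 5 involve arm-by-x. Only those 5 concern moderation.

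**3. Separable form.** The arm difference is [g_2(j) − g_1(j)] + [h_2(x) − h_1(x)]. The second bracket varies with x unless h_2 and h_1 differ by a constant, so the form permits what its description excludes. It also has no x-by-time term.

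**4. Simulation with baseline as a modelled occasion.** 54 participants, five visits, random intercept, linear x, no arm-by-x effect, likelihood-ratio test, 600 replicates:

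| Variance of improvement explained by x, both arms | Stated comparison (9 df) | Arm-by-x terms only (5 df) |
|---|---|---|
| 0 | 6.7% | 6.2% |
| 5% | 25.5% | 5.3% |
| 10% | 54.2% | 7.7% |
| 20% | 92.3% | 6.8% |

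Monte Carlo error is about √(0.54 × 0.46 / 600) = 2.0 points. Repeat runs gave 26/54/93% and 29/52/91%.

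A second set-up used 52 participants and four occasions including baseline, with critical values from a simulated null distribution (in effect a parametric bootstrap). With x correlated r = 0.2, 0.3, 0.4, 0.5 with improvement (r² = 4, 9, 16, 25%), the stated comparison rejects:

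- linear f: 19.5, 44.6, 75.5, 94.9% (at level 0.10: 29.6, 57.0, 84.4, 97.4%)
- quadratic f: 13.6, 30.8, 59.3, 86.8%
- separable null: 20.8% rising to 95.7%
- corrected comparison and median-split contrast: about 5% throughout

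If x shifts only the level of the score, linearly, the stated comparison holds 5%. A common curved level effect gives 51.7% with quadratic f.

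**5. Simulation with change scores at the four post-treatment visits.**

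- Constant linear effect of x: absorbed by xB. Runs at 5/10/20% explained gave 7/6.5/8% and, in another, 4–5%; the simulated-null set-up gave 5.0%.
- Common effect fading over follow-up: 25/49/79% and 21/43/82% in two runs at 5/10/20%. With r = 0.5 at 1 week fading to zero at 6 months, 89.6%.
- Common non-linear effect: 65.9% with quadratic f.

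**The case against.** Five points can be made for the plan.

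- **The right target is named.** The text says the interest is in whether f_2 − f_1 is flat in x, and bootstrapping that contrast within the fuller model would be valid. This stands: the fault is a mismatch between target and test, not a wrong estimand. But the sentence that defines the test uses the reduced model.
- **The first step is sound.** The median-split contrast compares treatment effects directly, comes first, and has the most proximal post-treatment outcome as its main test. This stands. A reader might infer that Aim 2 as a whole cannot separate prognosis from moderation, or that prognostic factors will be reported as moderators. The documents do not support either: they can be so reported, and only from the second step.
- **The response is not fixed.** Four occasion labels against five scheduled assessments fit either a modelled baseline or change at four post-treatment visits with 1 week coded 0. A reader might take 26/54/92% as the error rate of the plan. It applies only to the first reading. On the second, a constant linear effect does no harm, though a fading or curved one does.
- **The index on h may be a slip.** The formula has arm 2 on the left and k on the right, and the description says no interaction is meant. That is plausible, and it is a correction of notation rather than strong evidence of a flawed null.
- **The aim is exploratory and also seeks predictors of response to SFA.** This lowers the priority. It does not justify labelling a mixed test as one of moderation.

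**Conclusion.** The concern holds for the second, model-based step of Aim 2. That the stated comparison is not a pure moderation test follows from the printed models and needs no simulation: shared x-by-time or non-linear x effects make the simpler model false while f_2 − f_1 stays flat. The same is true on either reading of the response.

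The size does rest on assumptions. At a nominal 5%, with x explaining 5, 10 or 20% of the variance equally in both arms, false rejection is roughly 26, 54 and 92% if baseline is modelled. On change scores at the four post-treatment visits it stays near nominal for a constant linear effect, rises to roughly 20–25, 45 and 80% for a common effect that fades, and is also inflated by a common non-linear effect. The separable form needs correcting as well. The primary analysis, the sample size and the median-split contrast are untouched.

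**What to change.** - Keep the same arm-common function m(j,x) in both models: compare u + m(j,x) + q_k(j) with u + f_k(j,x), so that only the arm-by-x and arm-by-x-by-time terms are tested. Alternatively, bootstrap the f_2 − f_1 contrast directly and test whether it is flat in x.
- Make m as flexible in x as f_k. If the true effect is curved and both models hold only linear x, even the corrected comparison rejected 8.9–10.1%; with quadratic terms in both it returned to 4.9–5.2%.
- Write the separable form as g_k(j) + h(x), with no arm index on h. Do not read its rejection as moderation, because it still has no x-by-time term.
- State whether the response is score or change, and whether occasion 0 is baseline or the 1-week visit.

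The cost is model wording and code. No data collection, visit or sample size changes.

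### The first-line moderator test in Aim 2 cuts continuous moderators at the median, which costs about 36% of the information in that exploratory test; the second approach is not affected

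*Protocol*

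**What the plan says.** Section 7 of the Protocol, in the statistical analysis for Aim 2, lists the baseline moderators: lesion volume, lesion site, FA, MD, Fisher-transformed connectivity, WAB-R aphasia severity and PNT naming severity. All but lesion site are naturally continuous.

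For the first approach it states that "we will split moderating measures, such as the rs-fMRI Fisher Z-transformed measures of connectivity at the median values". The tDCS response difference is then compared between the lower and upper halves. On multiplicity: "A standard t-test contrast approach will be adjusted for multiplicity using Bonferroni corrections", because the moderators are analysed separately. The most proximal post-treatment outcome is the primary test.

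For the second, model-based approach it states: "This will not require dichotomizing the moderating variables and it will model the relationship non-parametrically". That approach can take several moderators together and has two variations, one that assumes linearity and one that is non-parametric.

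The sequence is fixed: "To summarize the approaches, we will proceed in this order". Item 1 is a "T-test comparing the treatment effect across median splits of the moderating variables performed separately, one at a time", and the spline-based models are item 2.

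The Secondary Objectives give the status of the aim: "This exploratory aim may identify stroke patients who are mostly likely to benefit from cerebellar tDCS and/or SFA". The Protocol states no power, number of tests or significance level for moderation.

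**The concern.** Cutting a continuous moderator at its median treats two patients just either side of the cut as different and two patients at opposite ends of one half as alike. If the tDCS effect changes steadily with the moderator, this discards information and lowers the power of the interaction test. The sample is already small for interactions, and Bonferroni lowers power further.

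The plan chooses the 1-week outcome for this test because power for moderation should be greatest there, then gives part of that power away through the split. It calls the split approach conservative. Bonferroni already controls the error rate, though, so the split adds no protection against false positives.

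At stake is whether the simplest of the planned moderator analyses makes reasonable use of the data when it looks for patients likely to benefit.

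**Working it through.** **1. The plan's own figure.** The Protocol states that "52 participants (26 per group) will give us 80% statistical power to detect 0.7 SD difference", and "This was done using Wald test for group assignment coefficient in linear regression at 0.1 level of statistical significance". With a two-sided test, n per arm = 2 × (1.645 + 0.842)² / 0.7² = 25.2, so 26. Power at 26 per arm is 81.0% by the normal formula and 80.1% by noncentral t. The figure reproduces. Attrition: 52 / 0.9 = 57.8, so 58 would be needed; 60 are enrolled and 60 × 0.9 = 54 complete. The 54 is derived, not stated.

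**2. Information kept by a median split.** Relative to a linear term, this is the squared correlation between the moderator and its above-median indicator. For a normal moderator it is 2/π = 0.637, a loss of 36.3%, so 54 participants act like 54 × 0.637 = 34. The loss depends on shape: 25% for a uniform moderator, about 52% for an exponential one and about 73% for a lognormal one with log-SD 1.

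**3. Smallest detectable interaction (80% power, n = 54, residual SD 1, 1:1).** The standard error of the interaction slope is 2/√54 = 0.272, in outcome SD per moderator SD. For the split, divide the detectable slope by √0.637 = 0.798.
- Two-sided 0.05: (1.960 + 0.842) × 0.272 = 0.76 continuous; 0.76 / 0.798 = 0.96 split.
- Two-sided 0.05/7: (2.690 + 0.842) × 0.272 = 0.96 continuous; 1.21 split.
- From 0.05/5 to 0.05/10: 0.93 to 0.99 continuous; 1.17 to 1.25 split.

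With the split, the tDCS effects in the two halves must differ by (1.960 + 0.842) × 4/√54 = 1.53 SD at 0.05, or 1.92 SD at 0.05/7. The trial is sized for a main effect of 0.7 SD.

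**4. Power by simulation (27 per arm, normal moderator, linear moderation).** The large-sample formula is optimistic at this size, so I simulated. A slope g corresponds to a difference between halves of 2g√(2/π) = 1.596g, so 0.44, 0.7 and 0.9 give 0.70, 1.12 and 1.44 SD.

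| Slope | Continuous, 0.05 | Split, 0.05 | Continuous, 0.05/7 | Split, 0.05/7 |
|---|---|---|---|---|
| 0.44 | 33% | 22–24% | 12% | 6–7% |
| 0.7 | 68% | 47–49% | 38–39% | 20–21% |
| 0.9 | 86% | 65–68% | 63–64% | 35–39% |

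The lower split figures arise when the moderator acts only in the tDCS arm. It then also has a prognostic main effect, which the split absorbs only partly. The upper ones arise when moderation is symmetric between the arms.

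**5. Imaging moderators.** The visit descriptions in section 4 limit MRI to participants who consent and have no contraindication. The size of that subset is not given. At an assumed n = 40 and slope 0.7, power is about 53% continuous against 37% split at 0.05, and 24% against 13% at 0.05/7.

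**Assumptions not in the Protocol:** the level 0.05 for Aim 2 (the only stated level, 0.1, is for the primary comparison), seven tests, the interaction sizes, normality and linearity.

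**The case against.** The strongest reply is that the plan already contains the better analysis. Step 2 does not dichotomise, one of its variations assumes linearity, and nothing makes it conditional on step 1. This stands, and it limits the point. A reader might infer that Aim 2 as a whole will miss real moderators or give no gradient of benefit. The documents do not support that. What is left is that the simple, one-moderator, Bonferroni-corrected test placed first is the inefficient one.

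A reader might also infer that step 2 lacks multiplicity control and so cannot count. The Protocol attaches Bonferroni to step 1 because moderators are tested separately there. Step 2 can take them jointly and compare nested models, so it does not raise the same problem. The Bonferroni penalty is not part of the defect either, since it would apply equally to a continuous test.

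Sample size is the larger limitation. If the halves differ by 0.70 SD, as large as the effect the trial is powered for, power at 0.05 is only about 33% continuous against 22–24% split. The change helps but does not cure low power. This stands.

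If the true effect is a threshold near the median, the efficiency ratio reverses and the linear term keeps only about 64%. A split also limits the leverage of extreme values. Both are fair, but the Protocol does not posit a threshold.

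Two further inferences go too far. An observed median can be reported and applied as a cut in a Phase III trial, so the cut is not unusable. Lesion site has no natural median, but how it is coded is detail for the analysis plan, and the point here does not apply to it.

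**Conclusion.** The point holds as an inefficiency in the first of two exploratory moderator analyses. It is not an error in the sample size, and it does not touch the primary result. For a roughly normal moderator with linear moderation, step 1 discards about 36% of the available information. Over assumed slopes of 0.44 to 0.9 that lowers power by about 10 to 20 percentage points at 0.05, and by about 5 to 28 points at 0.05/7, with up to 54 completers. The figure of 54 fits the WAB-R and PNT moderators; for imaging moderators absolute power is lower.

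The direction does not depend on the assumed level or number of tests. It does depend on moderation being closer to a trend than to a step at the median. Because step 2 keeps moderators continuous and includes a linear version, the consequence is limited to the first-line, Bonferroni-corrected test. The change is worth making because it is cheap, but it is a modest improvement.

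**What to change.** In step 1 of Aim 2, replace the median-split t-test by a linear model of 1-week PNT change on group, the continuous moderator and group × moderator. Fit it for one moderator at a time and test the interaction with the Bonferroni correction already planned. Use median splits only to display results. If baseline covariates are added, leave out any that duplicates the moderator under test: baseline PNT when naming severity is tested, and WAB-R severity when aphasia severity is tested.

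The cost is a change of wording, with no new data, visits or participants. The downside is that step 1 then assumes a linear trend and is less efficient if the true effect is a threshold near the median. The non-parametric variation in step 2 checks for this.
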